#### Circulating inflammatory cytokines

2.11.20

Serum concentrations of interleukin-18 (IL-18), interleukin-1β (IL-1β), interleukin-6 (IL-6), tumor necrosis factor-alpha (TNF-α), C-reactive protein (CRP), and NLR family pyrin domain containing 3 (NLRP3) will be determined using ELISA kits from Jiangsu Enzyme Exemption Immunosorbent Assay Industrial Co., Ltd. (MM-0139H1, MM-0181H1, MM-0049H1, MM-0122H1, MM-0135H1, and MM-51822H1, respectively). The specific experimental procedures will be carried out in strict accordance with the instructions provided with the kits.

#### Central fatigue biomarkers

2.11.21

Serum levels of 5-hydroxytryptamine (5-HT), dopamine (DA), and gamma-aminobutyric acid (GABA) will be measured by ELISA using kits from Nanjing SenBeijia Biological Technology Co., Ltd. (SBJ-H0191-96T, SBJ-H1796-96T, and SBJ-H1124-96T, respectively). The specific experimental procedures will be carried out in strict accordance with the instructions provided with the kits.

#### Catecholamines

2.11.22

Serum levels of noradrenaline (NA) and adrenaline (A) will be quantified using ELISA kits from Nanjing SenBeijia Biological Technology Co., Ltd. (SBJ-H0141-96T and SBJ-H0965-96T, respectively). The specific experimental procedures will be carried out in strict accordance with the instructions provided with the kits.

#### Energy metabolism biomarkers

2.11.23

Serum levels of Sirtuin 1 (Sirt1), Forkhead box O3 (FOXO3), and Perilipin 2 (PLIN2) will be determined by ELISA using kits from Jiangsu Enzyme Exemption Industry Co., Ltd. (MM-13492H1, MM-0310H1, and MM-60717H1, respectively). Concurrently, serum cortisol levels will be measured using a kit from Nanjing SenBeijia Biological Technology Co., Ltd. (SBJ-H0998-96T). The specific experimental procedures will be carried out in strict accordance with the instructions provided with the kits.

### Statistical analysis

2.12

All statistical analyses will be performed using R software (version 4.3.1 or later; R Foundation for Statistical Computing, Vienna, Austria). For the description of baseline data, normally distributed continuous variables will be presented as 
mean±standard deviation (SD), while non-normally distributed variables will be reported as median [interquartile range (IQR)]; categorical variables will be expressed as frequencies and percentages (n, %). For the comparison of baseline data between groups, independent samples t-tests will be used for normally distributed continuous variables, the Mann-Whitney U test will be used for non-normally distributed data, and the chi-square (χ²) test or Fisher’s exact test will be used for categorical data.

Efficacy analyses will be conducted according to the intention-to-treat (ITT) principle and will include all randomized participants. Continuous outcomes, including NMD and GWE, will be analyzed using linear mixed-effects models (LMMs). To rigorously control for potential confounding, background medication use will be prespecified and included as fixed-effect covariates in the models. Medications will be categorized by therapeutic class, with binary indicators (yes/no) created for: (1) glucose-lowering agents (with separate indicators for GLP-1 receptor agonists and SGLT2 inhibitors), (2) antihypertensive medications, and (3) statins. Each LMM will incorporate group, time, and the 
group×time  interaction as fixed effects, with a random intercept for each participant to account for repeated measurements.

Sensitivity analyses will be performed using multiple imputation to assess the robustness of the findings under different assumptions regarding missing data. In addition, a per-protocol (PP) analysis will be conducted as a secondary sensitivity analysis, including only participants with an attendance rate of at least 80%. Secondary outcomes will be considered exploratory and hypothesis-generating; therefore, no adjustment for multiple comparisons will be applied. A two–tailed *P*–value < 0.05 will be considered statistically significant.

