### Sample size calculation

2.5

The sample size calculation is based on the two co-primary outcomes: NMD and GWE. The calculation is for a superiority trial, designed to achieve 80% statistical power at a two-sided significance level (α) of 0.05. No adjustment for multiplicity was applied to the co-primary outcomes (NMD and GWE) because they represent distinct physiological domains and address separate, independent research questions. NMD assesses the structural integrity and function of peripheral vascular smooth muscle (endothelium-independent pathway), whereas GWE serves as a specific metric for central myocardial energetics and metabolic efficiency. In the pathophysiology of T2DM, peripheral vascular remodeling and myocardial metabolic inflexibility are distinct complications that may progress asynchronously and respond to intervention via different mechanisms. Therefore, to capture the distinct effects of aerobic exercise on these independent physiological systems, each outcome was evaluated at a two-sided significance level of 0.05. All calculations were performed using PASS (Power Analysis and Sample Size) software. For GWE, as no direct data on the effects of AE exist, parameters are derived from a study on the effects of GLP-1 receptor agonists (GLP-1 RAs) in patients with T2DM. We hypothesized that the effect of AE would be 75% of that observed with GLP-1 RA treatment (20). This yields an estimated mean between-group difference (δ) of 2.7% with a projected standard deviation (σ) of 4.0%. This corresponds to a standardized effect size (Cohen’s d) of approximately 0.68, representing a “moderate-to-large” effect size. This estimation is considered conservative given that lifestyle and exercise interventions have previously demonstrated comparable or superior efficacy to medical interventions in key physiological domains. For example, the Diabetes Prevention Program showed that lifestyle intervention was more effective than metformin for the metabolic profile (21).

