Based on these parameters, a minimum of 34 participants per group (n=68 total) is required to detect a significant difference. For NMD, the estimation is based on data from Ziegler et al., we estimated a mean intervention effect (δ) of 4.0% with a standard deviation (σ) of 5.6% (22). This calculation requires a minimum of 32 participants per group (n=64 total). To adequately power the study for both co-primary outcomes, we will use the larger of the two estimates. Therefore, the sample size is driven by the requirements for NMD. To account for a potential 10% dropout rate, we will recruit 37 participants per group, bringing the total sample size to 74.

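### Background medication entered only as main effects leaves the group-by-time estimate essentially unadjusted, so the stated control of confounding is not delivered

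*Protocol article*

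**What the plan says.** The primary outcomes are changes in NMD and GWE from baseline to week 12 (Abstract, Methods), and both are measured only at those two visits (section 2.1 and Table 1).

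Section 2.12 gives the analysis model. On medication it states: "To rigorously control for potential confounding, background medication use will be prespecified and included as fixed-effect covariates in the models". The indicators are yes/no by therapeutic class: glucose-lowering agents (with GLP-1 receptor agonists and SGLT2 inhibitors coded separately), antihypertensives and statins. The rest of the model is group, time and the group-by-time "interaction as fixed effects, with a random intercept for each participant to account for repeated measurements". No medication-by-time term is named, and the baseline outcome value is not a covariate.

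Three other passages bear on this. Section 2.3 requires a stable regimen for at least three months before entry. Section 2.7 requires the regimen to be kept for the 12 weeks, with dose changes only for safety. Section 2.6 specifies simple randomisation.

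**The concern.** The tested effect is a contrast in change, while the medication terms act on level. A covariate that has the same value at both visits shifts both visits equally and so cannot explain why one participant changes more than another. The terms would appear in the model, and the report could call the result medication-adjusted, although the estimate is numerically close to, or identical with, the one obtained without them.

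This matters if users of some drug class change differently over 12 weeks and the arms happen to differ in use of that class. Simple randomisation of 74 people allows such differences, and the planned terms would not remove their effect.

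**Working it through.** **Scale, from section 2.5.** The design is "designed to achieve 80% statistical power at a two-sided significance level (α) of 0.05". Using n per arm = 2(1.960 + 0.842)²/d²:

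- GWE: "mean between-group difference (δ) of 2.7% with a projected standard deviation (σ) of 4.0" per cent, so d = 2.7/4.0 = 0.675 and n = 15.70/0.4556 = 34.5, that is 35 (36 by the t distribution). The plan has 34.
- NMD: "we estimated a mean intervention effect (δ) of 4.0% with a standard deviation (σ) of 5.6" per cent, so d = 0.714 and n = 15.70/0.510 = 30.8, that is 31 (32 by t). The plan has 32.
- Dropout: 34/0.9 = 37.8, that is 38 per arm. The plan has 37: "To account for a potential 10% dropout rate, we will recruit 37 participants per group, bringing the total sample size to 74".

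These figures agree to within one or two per arm. The present point does not depend on them; it uses only 37 per arm, the 2.7-point effect, the SD of 4.0 and the 10% dropout.

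**Algebra.** For participant i at visit t (0 or 1), the written model is

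y = β0 + β1·group + β2·t + β3·group·t + γ·med + u + e.

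The within-person change is

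y(1) − y(0) = β2 + β3·group + e(1) − e(0).

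Both u and γ·med cancel. The within-person mean carries no separate information on β3, because β0 and β1 are free. So with complete pairs the estimate of β3 is the difference between arms in mean change, with or without the medication terms, whatever the data. A participant with a baseline value only adds some between-person information, so with dropout the estimate can move a little.

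**Simulation.** There were 2,000 trials per scenario, 37 per arm, fitted by REML. The true effect of 2.7 and SD of 4.0 come from section 2.5. All else is assumed: within-person correlation 0.5, five indicators with prevalence 0.2 to 0.8, and a 2-point effect on change for each of two classes. A 20-point imbalance in every indicator should then add 2 × 0.20 × 2 = 0.8. The mean group-by-time estimates were:

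| Scenario | No medication terms | Main effects, as written | With medication × time |
|---|---|---|---|
| Complete pairs, no built-in imbalance | 2.68 | 2.68 | 2.69 |
| Complete pairs, 20-point imbalance | 3.48 | 3.48 | 2.69 |
| 10% dropout, 20-point imbalance | 3.52 | 3.52 | 2.73 |
| 20% dropout, 20-point imbalance | 3.54 | 3.54 | 2.71 |
| 10% of participants switch one class, 20-point imbalance | 3.47 | 3.54 | 2.88 |

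- Complete pairs: adding the main effects moved the estimate by at most about 1e-13 (rounding error).
- 10% dropout: the shift had SD 0.07, with 95% of shifts within 0.14, against a standard error of about 1.0. None of the imbalance effect was removed.
- Standard error, complete pairs: essentially unchanged at correlations of 0.5 and 0.8; it moved by up to 11% at 0.1, while the estimate still did not move.

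A second simulation (400 trials; assumed use 40% against 20%, users changing 3.0 points more, 10% dropout, true effect 2.7) gave 3.39 without medication terms, 3.39 as written, 2.75 with medication × time and 2.77 with ANCOVA.

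**How likely is imbalance?** At an assumed prevalence of 30% and 37 per arm, the difference in use has SD √(2 × 0.3 × 0.7/37) = 0.107. A difference of 20 points or more occurs in about 6% of trials, and the median difference is about 8 points. Across five independent indicators with assumed prevalences of 0.2 to 0.8, at least one differs by 20 points or more in about 27% of trials.

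**Cost in precision.** Assume 30% users, users changing 3.0 points more, and a residual SD of change of 4.0. The SD of change is then √(16 + 9 × 0.21) = 4.23, and the standard error 4.23 × √(2/37) = 0.98. Power for 2.7 is about 78%. With the medication effect fully removed, the standard error is 4.0 × √(2/37) = 0.93 and power about 82%. Type I error of the unadjusted comparison was 5.0% in 40,000 simulated trials.

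**The case against.** The strongest reply is that randomisation already protects the comparison. Medication does not confound it in expectation, the unadjusted test holds its 5% level, and chance imbalance is part of what that test allows for. This stands. A reader might infer from the cancellation that the primary analysis is biased; the documents do not support that, because allocation is random (section 2.6).

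A reader might also take 0.6 points as the bias of this trial. It is 0.20 × 3.0, the product of two assumptions, and neither number is in the protocol. At the median imbalance the figure would be about 0.08 × 3.0 = 0.24. Nor does the GLP-1 receptor agonist source for the GWE effect show that users will drift. It implies a treatment effect of 2.7/0.75 = 3.6 points in that source, whereas participants here must already have been stable for three months and must keep their regimen. Those rules, and the planned baseline comparison of the arms, make a large differential change less likely.

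Finally, a reader might say that the terms cannot move the estimate at all. That is exact only with complete pairs and constant indicators. Section 2.5 expects dropout, and section 2.12 does not say outright that indicators are fixed at baseline. In the simulations neither departure made the main effects remove imbalance.

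None of this rescues the sentence itself. It claims an adjustment that the model beside it does not make.

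**Conclusion.** The concern holds as a mismatch between claim and model. As written, the medication main effects leave the group-by-time estimate equal to the unadjusted difference in mean change: exactly so with complete pairs and constant indicators, and up to noise of about 7% of its standard error with 10% dropout under the assumed inputs. Any chance imbalance in medication that is related to change stays unadjusted.

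The estimate remains unbiased in expectation. Under the stated assumptions the loss is about four points of power, the missing protection when an imbalance does arise, and an inaccurate statement of control. Severity: should be fixed before unblinding. It is not a threat to the validity of the trial.

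**What to change.** State in section 2.12 that the medication indicators take their baseline values, and let them act on the tested contrast in one of two ways:

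- ANCOVA of the week-12 value on group, baseline value and baseline medication indicators; or
- the planned mixed model with medication-by-time terms added.

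The second keeps participants who have only a baseline value in the model. A plain ANCOVA uses those with a week-12 value, so the text should say how missing values are handled. Either route costs wording and about five degrees of freedom.

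If the sponsor prefers to keep the model as it is, the claim that it rigorously controls for medication should be deleted and the result described as unadjusted for medication effects on change. Recruitment is ongoing, so the choice can still be made before unblinding; made afterwards, it would be post hoc for both co-primary outcomes.

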**Methods:**

This study is a randomized, single-assessor-blind, parallel-group, two-arm controlled trial that will enroll 74 patients with T2DM. Participants will be randomly assigned in a 1:1 ratio to either a 12-week supervised aerobic exercise group (55–75% of HR_peak_, three times per week) or a non-exercise control group. The primary outcomes are the changes from baseline to 12 weeks in NMD and GWE. Secondary outcomes include key cardiometabolic indicators (energy metabolism, insulin levels), office and 24-hour ambulatory blood pressure, cardiovascular risk factors, 24-hour movement behavior, cardiopulmonary function, arterial stiffness (baPWV), vascular endothelial function (FMD), cardiac electrical activity, echocardiographic parameters, and self-reported fatigue. Additional exploratory variables include markers of myocardial injury and skeletal muscle injury, circulating markers of oxidative stress and inflammation, central fatigue biomarkers, and levels of cardiovascular-related hormones. Recruitment began in June 2025 and is currently ongoing.

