### Research design

2.1

This study is a single-assessor-blind, parallel-group, two-arm randomized controlled trial. Participants will be randomly assigned in a 1:1 ratio to either a 12-week aerobic exercise group (AE group) or a non-exercise control group (Con group). Clinical assessments will be performed at baseline (pre-intervention) and at the 12-week follow-up. A detailed schedule of enrollment, interventions, and assessments is presented in **Table 1**. Considering the minimum clinically effective dose of exercise, adherence to the intervention will be defined as the completion of at least 80% of the prescribed exercise sessions. Participants who do not meet this threshold will be categorized as non-adherent. To minimize attrition bias, all participants, regardless of their adherence or completion of the intervention, will be followed up and included in the primary analysis according to the intention-to-treat (ITT) principle. Written informed consent will be obtained from all participants before enrollment. The reporting of this trial will adhere to the Consolidated Standards of Reporting Trials (CONSORT) statement.

**Table 1 T1:** Participant timeline: schedule of enrollment, interventions, and assessments.

Trial period	Enrollment		Post-randomization			Close-out
Timepoint	Screening *(Day-12 to 0)*	Baseline *(Day0)*	Intervention Period *(Weeks 1-6)*	Intervention Period *(Day42)*	Intervention Period *(Weeks 6-12)*	*Week 12 (± 3 days)*
Enrollment:						
Eligibility screen	X					
Informed consent	X					
Medical history	X					
Randomization		X				
Intervention:						
Aerobic Exercise Group		X				X
Control Group		X				X
Assessments:						
Primary outcomes						
nitroglycerin-mediated dilation		X				X
myocardial global work efficiency		X				X
Secondary outcomes						
Energy Metabolism		X				X
Peak Heart Rate (HR_peak_)		X		X		X
Traditional Cardiovascular Risk Factors		X				X
Cardiovascular & Cardiopulmonary Function		X				X
Self-reported fatigue assessment		X				X
24-hour physical activity monitoring		X				X
Circulating biomarkers		X				X
Safety monitoring						
Adverse Events		X				X

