### Random assignment and blinding

2.6

Following baseline assessments, participants will be randomly assigned in a 1:1 ratio to either the AE group or the Con group. The randomization sequence will be generated using a computer-based random number generator (Microsoft Excel) by an independent statistician who is not involved in participant recruitment or data collection, employing a simple randomization method. Allocation concealment will be maintained using sequentially numbered, opaque, sealed envelopes. These envelopes will be kept by a designated research assistant and will be opened only after baseline assessments are completed, thereby minimizing selection bias.

This study employs a single-assessor-blind design. To maintain the blind, a rigorous single-blinded assessor design will be implemented where all participants are assigned unique alphanumeric identification codes for data collection and analysis. Specifically, imaging specialists (echocardiographers and vascular technicians) will perform scans and post-processing analyses using only these codes, and will be strictly trained to refrain from discussing intervention allocation or personal perceptions of improvement with participants during examinations to prevent inadvertent unblinding. Similarly, biochemical analysts will process blood samples labeled solely with identification codes, ensuring they remain unaware of group allocation or sampling time points. Furthermore, statistical analysis will be conducted by an independent statistician using de-identified datasets with dummy group labels. Access to unblinded data will be restricted exclusively to the clinical exercise physiologists delivering the intervention and the Data Safety Monitoring Board responsible for monitoring adverse events. This design ensures methodological rigor, minimizes bias, and enhances the reliability and validity of the study findings.

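### The primary mixed model leaves baseline means free in each arm, so it acts as a change-score analysis: valid, but less precise than one using the baseline NMD and GWE already collected

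*Protocol article*

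**What the plan says.** The Abstract defines the endpoint: "The primary outcomes are the changes from baseline to 12 weeks in NMD and GWE". Research design gives two assessment times: "Clinical assessments will be performed at baseline (pre-intervention) and at the 12-week follow-up". Random assignment and blinding puts allocation after the baseline measurements: "Following baseline assessments, participants will be randomly assigned in a 1:1 ratio to either the AE group or the Con group".

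Statistical analysis then fixes the model for continuous outcomes, NMD and GWE included: "Each LMM will incorporate group, time, and the" group×time "interaction as fixed effects, with a random intercept for each participant to account for repeated measurements". The only other covariates named are drug classes: "background medication use will be prespecified and included as fixed-effect covariates in the models". Baseline NMD or GWE is not listed as a covariate, and no common baseline mean is imposed.

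The trial is "designed to achieve 80% statistical power at a two-sided significance level (α) of 0.05". For GWE, Sample size calculation assumes an "estimated mean between-group difference (δ) of 2.7% with a projected standard deviation (σ) of 4.0" (percentage points). For NMD it assumes a difference of 4.0 with an SD of 5.6.

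**The concern.** The group main effect lets the arms have different baseline means. Because randomisation follows the baseline assessment, the true means are equal by design, so this parameter estimates something known to be zero. With two visits, group×time then becomes the plain difference in mean change. A change score subtracts the whole baseline value, whereas the best linear adjustment subtracts only the part that predicts week 12.

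The medication indicators do not make up for this. Entered as main effects that are constant over time, they leave the group×time estimate unchanged when data are complete. The plan therefore adjusts for covariates that do not move the primary contrast and omits the one measurement most likely to sharpen it.

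What is at stake is precision, in a trial fixed at 74 participants and already recruiting, not validity.

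**Working it through.** **Inputs.** From Sample size calculation: GWE δ = 2.7, σ = 4.0; NMD δ = 4.0, σ = 5.6; two-sided α = 0.05; 37 recruited per arm; 10% dropout. Evaluable per arm: 37 × 0.9 = 33.3, taken as 33. Assumptions: r is not given, so 0.3 to 0.8 is shown. The article does not say whether σ is an SD of change or of a single visit, so both readings are shown. The SD is taken as equal at the two visits unless stated.

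**The plan's own figures.** With n = 2(1.96 + 0.84)²σ²/δ² and unrounded normal quantiles:
- GWE: 34.5, rounded up to 35 (34 if d is first rounded to 0.68), against 34 stated.
- NMD: 30.8, rounded up to 31 (32 by the t-test), against 32 stated.

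Both are close enough to use the stated inputs.

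**Is the planned contrast a change score?** The stated model, with five medication indicators, was fitted to simulated two-visit data. In one complete data set the group×time estimate was 0.75417 (SE 0.25170), and the difference in mean change gave the same values. Over 300 complete data sets at each of r = 0.3, 0.5 and 0.7, the two agreed to six decimals. With 10% of week-12 values missing they differ slightly.

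**Variance.** Let s be the single-visit SD. Per participant:
- change score: 2s²(1 − r)
- baseline-adjusted: s²(1 − r²)
- ratio: (1 − r²) / [2(1 − r)] = (1 + r)/2

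This gives 0.65, 0.75, 0.85 and 0.90 at r = 0.3, 0.5, 0.7 and 0.8. Simulated ratios (constrained model to planned model) were 0.67, 0.76 and 0.86 at the first three values with complete data, and 0.69, 0.78 and 0.88 with 10% missing.

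**Power at 33 per arm** (non-central t, 64 df).

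σ read as an SD of change; adjusted SD = σ√((1 + r)/2):

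| r | GWE planned | GWE adjusted | NMD planned | NMD adjusted |
|---|---|---|---|---|
| 0.3 | 77% | 92% | 82% | 94% |
| 0.5 | 77% | 88% | 82% | 91% |
| 0.7 | 77% | 83% | 82% | 87% |
| 0.8 | 77% | 81% | 82% | 85% |

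Example, GWE at r = 0.5: adjusted SD = 4.0 × √0.75 = 3.46.

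σ read as a single-visit SD; planned SD = σ√(2(1 − r)), adjusted SD = σ√(1 − r²):

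| r | GWE planned | GWE adjusted |
|---|---|---|
| 0.3 | 63% | 81% |
| 0.5 | 77% | 88% |
| 0.7 | 94% | 97% |
| 0.8 | 99% | 99% |

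**Unequal variances.** If the week-12 SD is k times the baseline SD, the ratio is k²(1 − r²)/(1 + k² − 2rk). At k = 1.25 and r = 0.7 this is 1.5625 × 0.51 / (2.5625 − 1.75) = 0.98, so almost nothing is gained there.

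**Can one simply delete the group term?** A random intercept forces equal variance at the two visits. Null simulations at 33 per arm and r = 0.5, with k = 0.8, 1.0, 1.25 and 1.5 (assumed values; the article gives none), gave these rejection rates for the constrained random-intercept model in two separate runs: 2.3 and 2.8%, 5.2 and 5.0%, 7.6% in both, 9.1 and 9.4%. The planned model gave 5.0, 4.5, 5.0 and 5.4%. ANCOVA stayed at about 5%.

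**The case against.** The strongest reply is that nothing here is an error. The endpoint is change from baseline, the model estimates the difference in change, and under randomisation it is unbiased with its type I error intact. That stands. A reader might infer that the primary analysis is biased or invalid, and the article does not support this. A chance baseline difference does pass into the estimate, but this holds only conditionally on the realised imbalance and averages to zero over randomisation.

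A reader might also infer that the simple randomisation described in Random assignment and blinding makes outcome imbalance at baseline more likely. The article does not show that. Blocking balances arm sizes, not baseline NMD or GWE, and stratification would help only on a factor correlated with them.

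The gain is also uncertain. It depends on an unstated r, vanishes as r approaches 1, and can nearly disappear if week-12 values are more variable. The planned GWE power is only slightly short on the SD-of-change reading (77% at 33 per arm, 82% if all 37 are evaluable), and NMD is at 82%. On the single-visit reading with r of 0.7 or more, the planned model is already comfortable. All of this limits the size of the point.

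Finally, the remedy is not free of risk. The random-intercept shortcut can inflate type I error. ANCOVA on observed cases loses participants without a week-12 value, so it is not interchangeable with the constrained model under dropout. Both objections stand and shape the fix.

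What remains is that the model is stated explicitly, so this is not a detail left to an unseen plan. It omits a design-justified adjustment that needs no new data.

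**Conclusion.** The point holds as one of efficiency. With two visits the stated model gives the difference in mean change, exactly with complete data and nearly so with 10% dropout. It forgoes the precision available from the baseline outcome. With equal visit variances, the effect's variance could be 35% lower at r = 0.3, 25% at 0.5, 15% at 0.7 and 10% at 0.8.

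If 4.0 is an SD of change, adjustment takes GWE at 33 per arm from just under the protocol's 80% target to above it throughout r = 0.3 to 0.8. If 4.0 is a single-visit SD, the benefit is large at low r and negligible at 0.8. These figures rest on assumed r, equal variances and 33 evaluable per arm. The change should be made, but the planned analysis would still be valid without it.

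**What to change.** Make one of these the primary analysis for NMD and GWE, and fix the choice before unblinding:

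1. A constrained longitudinal model: one baseline mean common to both arms, with time and group×time as fixed effects, and an unstructured 2×2 covariance in place of the random intercept. It keeps every randomised participant with a baseline value, in line with the intention-to-treat commitment.
2. ANCOVA of the week-12 value on group and its own baseline value, with multiple imputation for missing week-12 values. The article already plans multiple imputation as a sensitivity analysis.

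Do not merely delete the group term from the random-intercept model. Keep the medication covariates, name the tested contrast, and retain the unconstrained model as a sensitivity analysis.

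The estimand, the between-group difference in change at week 12, is unchanged. The cost is a wording change and either one degree of freedom (ANCOVA) or one extra covariance parameter (three in the unstructured matrix against two in the random-intercept model). No new data or participants are needed.
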